### Plans for collection, laboratory evaluation, and storage of biological specimens for genetic or molecular analysis in this trial/future use {33}

Not applicable. No biological specimens were collected.

## Statistical methods

### Statistical methods for primary and secondary outcomes {20a}

We will develop a detailed statistical analysis plan (SAP) which will be made available on the trial registry prior to conducting the primary statistical analysis. Stata 17 [21] will be used for all analyses.

Descriptive statistics will be used to compare the baseline characteristics of general practices, GPs, and patients between the three arms. Primary analysis will be intention to treat (ITT) where all general practices and their patients who receive NBCSP kit during the intervention period as determined at the beginning of the trial period will be analysed in the arm that they were allocated to, regardless of whether they received all or part of the intended intervention. For the primary outcome, logistic regression and generalised linear model with an identity link function and binomial family (when appropriate) will be used to estimate the odds ratio (relative measure) and difference in proportions (absolute measure) of each intervention compared to the control arm, and Intervention 1 compared to Intervention 2. Both regression models will use generalised estimating equations with robust standard errors to allow for clustering by general practice and will adjust for geographical remoteness (metropolitan/larger regional and rural/smaller regional) and state (Queensland and Victoria). Estimates of the intervention effect will be reported as both differences in the proportion (absolute measures) and odds ratio (relative measure) for each pair-wise comparison (control vs SMS only, control vs SMS bundle, SMS only vs SMS bundle) with respective 95% confidence interval and an overall *p*-value value testing the global null hypothesis of no difference in the proportion of eligible patients who return their FIT kit within 6 months of the due date across the three arms. No adjustments will be made for the multiple comparisons [22].

We will also estimate the intra-general practice correlation coefficient for the primary outcome, which quantifies the proportion of the true total variation in the outcome attributable to between-cluster variation, and this will be estimated and reported with 95% confidence intervals.

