#### Sample size {14}

Sample size was based on 80% power for an overall two-sided significance level of 5% (alpha), and an intraclass correlation coefficient (ICC) of 0.01. Planned primary comparisons are the two intervention arms (SMS only and SMS bundle) with the control arm, respectively, and the SMS only intervention with the SMS bundle. The Holm-Bonferroni correction was used to control the family-wise error rate across three pairwise comparisons. Thus, for the purposes of the sample size calculations, we conservatively set the alpha at 0.017. We assumed that 34% of patients in the control arm will have completed their FIT, based on the National screening data [20]. Sixty-three practices with an average of 260 of eligible patients per practice (standard deviation = 197; range 51 to 753; coefficient of variation = 0.76) [15] will be sufficient to detect a difference of 10% absolute increase in participation in the NBCSP within 6 months from when the NBCSP kit is due between each intervention arm (SMS only and SMS bundle) and control arm (44% vs 34%), respectively; and to detect a smaller difference of 7.5% (44% vs 51.5%) between the SMS only and SMS bundle intervention arms. The total of 63 practices allows for an additional practice per arm for potential loss of practices due to closures or merges. A national 10% increase in screening participation would prevent 27,000 bowel cancers and 16,800 deaths and is associated with an additional $200 million in costs over current screening levels over the next 20 years [4]. We anticipate that adding the weblinks to motivational and instructional videos in the SMS would have a smaller additional effect on increasing screening participation compared to a SMS only.

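### The sample size claims Holm-Bonferroni control at an overall 5% across three primary comparisons, but the analysis section declines any adjustment and sets no gate, so that 5% does not hold for the analysis as written

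*Protocol article*

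**What the plan says.** The Hypotheses section lists three primary hypotheses: SMS only against usual care, SMS bundle against usual care, and bundle against SMS only. Sample size {14} treats the same three as the planned primary comparisons and makes an explicit error-rate claim:

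- "Sample size was based on 80% power for an overall two-sided significance level of 5% (alpha), and an intraclass correlation coefficient (ICC) of 0.01"
- "The Holm-Bonferroni correction was used to control the family-wise error rate across three pairwise comparisons"
- "for the purposes of the sample size calculations, we conservatively set the alpha at 0.017"

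Statistical methods {20a} describes the primary analysis of those comparisons. Each pair gets a difference in proportions and an odds ratio with a 95% confidence interval. There is also one overall p-value for the null of no difference among the three arms. The paragraph closes with "No adjustments will be made for the multiple comparisons", supported by a citation. It does not say that the pairwise results are read only if the global test is significant, and it does not mention the Holm-Bonferroni procedure named in {14}.

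**The concern.** Holm-Bonferroni is a rule for judging ordered p-values. It controls error only if the analysis applies it; sizing a trial at a smaller alpha buys power and controls nothing. A protocol that claims family-wise control in one section and declines adjustment in another leaves its decision rule open.

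The practical risk is a comparison whose result lies between the two standards. Under Holm the smallest of the three p-values must fall below 0.05/3 = 0.0167. A 95% interval that excludes zero needs only p < 0.05. A result between these limits could be presented as confirmed under {20a} and not confirmed under {14}. The comparison most exposed is bundle against SMS only, where the protocol expects the smaller effect. If the rule is chosen after the data are seen, readers cannot tell whether the choice was neutral.

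**Working it through.** **Inputs, all from Sample size {14}:** overall two-sided alpha 5%; 0.017 per comparison; power 80%; ICC 0.01; mean 260 patients per practice; coefficient of variation 0.76; 44% v 34% and 44% v 51.5%; 63 practices, including one spare per arm, so 20 + 1 per arm.

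**1. Reproduce the planned size.**
- Design effect = 1 + [(0.76² + 1) × 260 − 1] × 0.01 = 5.09.
- The limiting comparison is 44% v 51.5%. Per arm before clustering, n = [z₁₋α/₂ √(2p̄(1−p̄)) + z₀.₈ √(p₁(1−p₁) + p₂(1−p₂))]² / (p₂ − p₁)². With alpha 0.017 this gives 924.
- Practices per arm = 924 × 5.09 / 260 = 18.1 by the normal formula.
- With t critical values on 2(k − 1) degrees of freedom for k practices per arm, 19 practices give 78.7% power and 20 give 81.3%.
- So 20 + 1 spare = 21 per arm, or 63 in all. The stated size is reproduced, and it was computed at 0.017.

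**2. Family-wise error of three unadjusted 5% comparisons.**
- With three equal arms, the largest pairwise |Z| exceeds 1.96 exactly when the range of the three standardised arm estimates exceeds 1.96 × √2 = 2.77.
- The studentised range distribution (3 groups, large sample) gives a probability of 12.2%. With t on 60 degrees of freedom it is 12.1%, and a simulation of 2 million draws gives 12.2%.
- Treating the comparisons as independent gives 1 − 0.95³ = 14.3%. This is too high, because the contrasts share arms.
- With unequal arm variances, up to 4:1, the figure stays between 11.9% and 12.2%.
- If exactly one pair is equal, only one true null can be rejected and the error is 5%. Exactly two true pairwise nulls cannot occur, because equality of two pairs forces the third.

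**3. The same error under the two remedies (all arms equal).**
- Holm-Bonferroni: 4.4%, and at most 5% in any configuration.
- Global test as a 5% gate, then pairwise tests at 5%: 5.0%. With three arms, any two pairwise nulls together form the global null, so this is a closed test.

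**4. Power under the remedies, 20 practices per arm.** Effective patients per arm = 20 × 260 / 5.09 = 1,021.

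| Comparison | alpha | Normal formula | t critical values |
|---|---|---|---|
| 44% v 51.5% | 0.0167 | 84% | 81% |
| 34% v 44% | 0.0167 | 99% | 98% |
| 44% v 51.5% | 0.05 | 92% | 91% |

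The first two rows are the first and strictest Holm step, so they are the lowest power that Holm can give. For the gate, the least favourable place for the third arm is midway between the other two. The global test then has noncentrality (0.075² / 2) / (0.248 / 1,021) = 11.6 and 87% power on 2 degrees of freedom. Passing both the gate and the 44% v 51.5% comparison then has about 85% to 87% probability by simulation. With the control arm at the planned 34%, it is about 92%.

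**The case against.** Leaving comparisons unadjusted is a respectable position when each answers its own question. Statistical methods {20a} adopts it deliberately and cites a source. Sample size {14} confines its 0.017 to the sizing. The only p-value {20a} names is the global one, and the pairwise results are planned as estimates with intervals. The SAP, promised before the primary analysis, is a natural place to settle the rule.

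Much of this stands, and it limits what can be said. Four stronger readings are tempting, and the document does not support them.

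- *The family-wise error is 12%, without qualification.* That figure needs all three arms to be equal and each hypothesis to be decided by its 95% interval.
- *The trial succeeds if any one comparison succeeds.* No such rule is stated; the three hypotheses are listed separately.
- *No scale is named as primary, so odds ratio and risk difference multiply the tests further.* The abstract and Outcomes {12} define the primary result as the difference in proportions, and {14} is sized on absolute differences. The odds ratio is a companion measure.
- *The trial is underpowered.* It was sized at the stricter alpha.

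The objection does not remove the contradiction. The three primary hypotheses are pairwise, so the global test alone cannot answer them. A 95% interval that excludes zero is equivalent to an unadjusted 5% test. No gate is stated, and {14} claims control of the family-wise rate in so many words. Declining adjustment is defensible; declining it while claiming an overall 5% level is not.

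**Conclusion.** The contradiction is real and lies in the current text; it is not a detail left for the SAP. As written, the overall two-sided 5% level in Sample size {14} is not a property of the analysis in Statistical methods {20a}. The family-wise error is about 12% when all three arms are equal and 5% when only one pair is. These figures assume that each hypothesis is judged by its own 95% interval, that the arms are of roughly equal precision, and that each single comparison holds its nominal 5%. Point estimates, intervals and sample size are unaffected. What is affected is the error-rate claim and the wording of conclusions for results between the two thresholds.

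**What to change.** Reconcile the two sections before the primary analysis, and carry the same rule into the SAP.

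- **Preferred:** replace the no-adjustment sentence in {20a} with Holm-Bonferroni at a family-wise two-sided 5%, applied to the three pairwise p-values for the difference in proportions. This matches {14}.
- **Equally valid:** make the planned global test a formal 5% gate, with the pairwise comparisons tested at 5% only if it is passed.
- **If unadjusted comparisons are kept:** remove the overall 5% family-wise claim from {14} and say that each comparison is judged on its own at 5%.

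Under either of the first two options, state that the 95% intervals are unadjusted estimates and that claims follow the adjusted test. Otherwise an interval could exclude zero while the test does not reject, with no agreed wording for that result.

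The cost is a sentence or two in the protocol and the SAP. No practices or patients are added, because the 63 practices were already sized at 0.017. (0.017 is 0.05/3 rounded up; the analysis should use 0.05/3.)

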### Interim analyses {21b}

No interim analysis is planned.

### Methods for additional analyses (e.g. subgroup analyses) {20b}

We will conduct a sensitivity analysis for the primary outcome; we will adjust for pre-specified baseline covariates, such as sex and age of the patient, and whether they have ever or never screened previously (according to the NCSR data). To address aim 2, we will conduct a sub-group analysis separately for each patient characteristic: age, sex, previous screening, and location of practice. For sub-group analysis we will include an interaction between patient characteristic and trial arm in the regression model described above for the primary analysis.

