#### The method (Fig. 4)

##### Step 1

The eligible patient list will be collected from each general practice EHR using a bespoke Structured Query Language (SQL) query. The list will be saved as a comma-separated values (.csv) file securely on the practice computer, with a name specific to the study identifier of the practice (practice ID) and the date of extraction (Dataset 1).

##### Step 2

The practice manager will add three columns of data including (1) a column with a Provider number for the principal GP for that practice, (2) a column with a unique trial ID code for each patient (e.g. GP0010001), and (3) a column with a unique practice ID code for each practice (e.g. GP001) (Dataset 2).

##### Step 3

This dataset will be saved as a.csv file and uploaded to the NCSR using a secure file transfer protocol (SFTP).

##### Step 4

Once the NCSR have the.csv file (Dataset 2), they will match the patients in the NCSR by date of birth, Medicare number, and name. The.csv file will be enriched with five additional columns of data for each person: one for the date they returned their last NBCSP kit (or blank if they have not returned one before) [‘Date_kit_returned’], one with the date their next NBCSP kit is due [‘Date_Kit_Due’], one if the NCSR cannot match patients’ identifying data with the register’s records [‘1’ if records match with NCSR database, ‘0’ if data in the.csv file does not match the register], one calculating the date the SMS will be sent [‘Date SMS is due’ which will be calculated as the (‘Date the NBCSP kit is due’ − 14 days)], and one calculating the patient’s age at the time when their kit is due [‘Age in months when kit is due’, which will be calculated as (= ‘Date the NBCSP kit is due’ − ‘Date of Birth’ in years, multiplied by 12)].

The NCSR will then save a.csv file (i.e. NCSR dataset) for every practice (Dataset 3).

##### Step 5

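### The primary model leaves previous screening, a register variable obtained before randomisation, to a sensitivity analysis and so gives up some precision at no saving

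*Protocol article*

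**What the plan says.** Under *Statistical methods for primary and secondary outcomes {20a}*, the primary outcome is analysed with a logistic model and, where appropriate, a binomial model with identity link. Both are fitted by GEE with robust standard errors for clustering by practice, and both "will adjust for geographical remoteness (metropolitan/larger regional and rural/smaller regional) and state (Queensland and Victoria"). These are the two randomisation stratifiers, and no other covariate is named.

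Under *Methods for additional analyses {20b}*, adjustment for patient characteristics is a sensitivity analysis: "we will adjust for pre-specified baseline covariates, such as sex and age of the patient, and whether they have ever or never screened previously". The same section uses age, sex, previous screening and practice location for subgroup analyses.

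Step 4 of *The method (Fig. 4)* lists the columns that the register adds to each practice's file. They include "one for the date they returned their last NBCSP kit (or blank if they have not returned one before") and age when the kit is due. According to *Sequence generation {16a}*, practices are allocated only after this enriched file has come back. Screening history is therefore a true baseline variable. The article gives no reason for keeping it out of the primary model.

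**The concern.** Whether someone returned an earlier kit is plausibly informative about whether they return the next one. The protocol itself treats it as a possible effect modifier. A prognostic covariate measured before allocation can be added to the primary model without risk of bias, and it narrows the confidence interval of the risk difference to the extent that it predicts the outcome.

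On the planned inputs most of the variance of an arm's return proportion is between practices. A covariate that also differs between practices could therefore be useful, and practice-level screening history is such a covariate. What is at stake is the width of the intervals, above all for SMS only v SMS bundle, which has the smallest target difference and the least spare power.

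**Working it through.** **Inputs from *Sample size {14}*.** "80% power for an overall two-sided significance level of 5% (alpha), and an intraclass correlation coefficient (ICC) of 0.01"; "we conservatively set the alpha at 0.017"; "We assumed that 34% of patients in the control arm will have completed their FIT"; "an average of 260 of eligible patients per practice"; "coefficient of variation = 0.76". The comparison that drives the size is 44% v 51.5%. One practice per arm is spare, so 20 of 21 are needed.

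**Step 1: reproduce the plan's figure, without covariates.**

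- Design effect = 1 + ((1 + CV²)m − 1) × ICC = 1 + (1.5776 × 260 − 1) × 0.01 = 5.09.
- Individually randomised n for 44% v 51.5%, alpha 0.017, 80% power: 924 per arm. Practices per arm = 924 × 5.09 / 260 = 18.1 by the normal formula.
- SE of the difference at 20 per arm = √[(0.2464 + 0.2498) × 5.09 / 5200] = 0.0220, so effect/SE = 0.075 / 0.0220 = 3.40.
- Power at 20 per arm: 84.4% (normal) or 81.3% (t, 38 df). At 19 per arm the t version gives 78.7%.
- So 20 is the smallest sufficient number on the t version, and (20 + 1) × 3 = 63. For 34% v 44%, power at 20 per arm is 98% to 99%.

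The stated size is met with no help from covariates.

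**Step 2: where the variance lies.** Between-practice share = 0.01 × 1.5776 × 260 / 5.09 = 4.10 / 5.09 = 81%. Within-practice share = 0.99 / 5.09 = 19%.

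**Step 3: possible gain.** The document gives no return rate by screening history, so the following are assumptions: 50% ever screened (40% to 60% changes little) and a return gap d of 20 to 50 points. Then R² = 0.25 d² / 0.2464. If screening history has the same ICC as the outcome (0.01), it explains the same share R² at both levels, and the SE is multiplied by √(1 − R²).

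| Gap d | R² | SE multiplier | Power, normal | Power, t |
|---|---|---|---|---|
| none | 0 | 1.00 | 84.4% | 81.3% |
| 20 points | 0.04 | 0.98 | 86.0% | 83.0% |
| 30 points | 0.09 | 0.95 | 88.0% | 85.2% |
| 40 points | 0.16 | 0.92 | 90.6% | 88.2% |
| 50 points | 0.25 | 0.87 | 93.8% | 91.8% |

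Power is for 44% v 51.5% at 20 practices per arm.

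**Step 4: less and more favourable cases.**

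- History explains only within-practice variation: variance falls by 0.19 × R², that is 0.8% to 4.9%, and the SE by about 0.4% to 2.5%.
- History clusters more strongly than the outcome (ICC 0.02): a simulation with 20 practices per arm gave SE ratios of 0.96 to 0.77 over the same gaps. With ICC 0.01 it gave 0.99 to 0.88. Neither showed bias.

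**Step 5: age.** The introduction gives 31.6% return at ages 50–54. Taking two equal halves averaging the assumed 34% (31.6% and 36.4%), R² = 0.25 × 0.048² / (0.34 × 0.66) = 0.003. Age alone adds almost nothing. No figure is given for sex.

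**The case against.** The strongest reply is that nothing here is wrong. Adjusting for the stratifiers matches the design, the adjusted analysis is pre-specified, and the trial reaches its stated power without it. Which model is called primary is a choice of efficiency. All of this stands.

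The size of the gain also rests on assumed inputs. The figures in the working compare with a model that has no covariates, whereas the planned model already contains state and remoteness. Any between-practice variance that these explain cannot be gained again.

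Four stronger readings are tempting, and the documents do not support them.

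- *The gain equals about a third more practices.* Take 40% ever screened, 65% v 15% return (R² = 0.4 × 0.6 × 0.5² / (0.35 × 0.65) = 0.26) and a quarter of between-practice variance explained. The variance ratio is then 0.19 × 0.74 + 0.81 × 0.75 = 0.75, and 1 / 0.75 = 1.33. None of these inputs is in the protocol.
- *The sensitivity analysis does not check the primary one.* For the odds ratio this is fair, because adding covariates changes it to a conditional quantity. The risk difference is collapsible, so for it the adjusted analysis is a proper check.
- *Chance imbalance will distort the result.* With 40% ever screened, the SD of the between-arm difference in that share is √(2 × 0.24 × 5.09 / 5460) = 2.1 points. Even a 50-point gap turns this into about 1 point on the effect. That is random error already inside the robust interval, not bias.
- *Ever/never must be replaced by a coding that separates first invitations from repeat non-responders.* Invitation history is not among the listed register columns, so the split could only be approximated from age. It is an option, not a requirement.

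**Conclusion.** The point holds as an avoidable loss of precision. The plan fixes a primary covariate set that omits a plausibly prognostic variable obtained before randomisation, and gives no reason. The analysis remains valid and adequately powered on its own assumptions.

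The direction of the gain is secure if screening history is prognostic, but its size is not. An SE reduction of about 2% to 13% assumes a 20 to 50 point gap and clustering like the outcome's. The reduction is below 3% if history works only within practices, and larger if it explains much of the between-practice variance. Power for SMS only v SMS bundle would rise by roughly 2 to 10 points. The comparisons with control have little to gain, since they already have 98% to 99% power. Nearly all the benefit would come from previous screening.

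**What to change.** Before unblinding, amend the protocol wording and write into the SAP:

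1. Primary model: arm, state, remoteness and previous kit return at patient level, preferably with the practice-level proportion who had returned a kit before. Age and sex may be added. State this as a closed list in place of the open-ended one in *{20b}*.
2. Report the marginal risk difference and marginal odds ratio by standardising the logistic GEE predictions, with standard errors that respect clustering by practice. The target then stays marginal when covariates are added, and non-convergence of the identity-link model no longer matters.
3. Keep the stratifier-only model as the sensitivity analysis, standardised in the same way so that the two results are directly comparable.

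The cost is wording and some analysis code. Kit return and age are already in the enriched file. Sex is not among the columns listed in Step 4, but the introduction says that it will be collected. No new data and no change to the conduct of the trial are needed.

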### Methods in analysis to handle protocol non-adherence and any statistical methods to handle missing data {20c}

A blinded review of the data will inform the approach for handling of missing outcomes. Supplementary analyses, including sub-group and adherence-adjusted analyses, handling of missing data, and sensitivity analysis to assess model assumptions including the robustness of the missing data assumption, will be detailed in the SAP.

